# An evidence-based tailored eHealth patient education tool for patients with knee osteoarthritis: protocol for a randomized controlled trial

**DOI:** 10.1186/s12891-022-05212-0

**Published:** 2022-03-22

**Keywords:** Osteoarthritis, Patient education, Telemedicine, Patient medication knowledge, Patient satisfaction

## Abstract

**Background:**

Osteoarthritis is a common and disabling condition that places heavy burden to individuals and healthcare systems. Patient education is a facilitator in the treatment decision making process, aiming to develop a treatment plan for the disease management. Electronic health (eHealth) is an alternative forum for the delivery of patient education and given the prevailing of eHealth in healthcare, introducing patient education programs using the technology has the potential to improve patient engagement, self-management and outcomes in patients with osteoarthritis. The study will evaluate the efficacy of eHealth patient education tool on patients’ perception of knee osteoarthritis and treatment options, satisfaction and compliance to treatments.

**Methods:**

This study is a prospective randomized controlled trial with a 1:1 allocation in two groups. We will recruit 216 patients diagnosed with knee osteoarthritis from the outpatient physiatry/physiotherapy clinic at West China Hospital, Sichuan University in Southwest China. Both groups will receive usual care and additionally, the intervention group will use eHealth patient education tool during the process. Measurements will be taken at baseline, post-intervention, 1 month, 3- and 6-months follow-up. Primary outcome will be patients’ knowledge about disease and treatment options, measured by the validated osteoarthritis patient knowledge questionnaire. Secondary outcomes include patients’ satisfaction with the consultation, the eHealth patient education tool, and their trust of the physiotherapist.

**Discussion:**

The eHealth patient education tool is designed to provide participants with an innovative model of care delivery and this trial will assess the efficacy of the tool and whether this new model of patient education will have the potential to increase patient knowledge and empower self-management. Results collected from this study will further inform future research employing eHealth tool as interventions for the management of a range of other chronic conditions and help participants in communities or rural areas having the equal access to health care services.

**Trial registration:**

This study was prospectively registered on the Chinese Clinical Trials Registry (ChiCTR2100051083) registered 12.09.2021.

**Supplementary Information:**

The online version contains supplementary material available at 10.1186/s12891-022-05212-0.

## Background

Osteoarthritis is a common and disabling condition that has an increasing health burden, with notable implications for people older than 60 years and healthcare systems [1]. Global percentage change in years lived with disability between 2006 and 2016 was 31.5% [2]. In China, around 61.2 million individuals had osteoarthritis recorded in 2017 [3, 4]. Treatment options range from non-pharmacological methods, such as education and self-management, physical activity and exercise, weight loss and physical modalities, to invasive treatments such as intra-articular injections and joint replacement surgery [1]. However, patients may be exposed to different benefits and risks receiving these treatments; therefore, the knowledge on osteoarthritis, how to manage, when and how to make decisions, should be incorporated into a discussion in the development of a treatment plan between physicians and patients.

Patient education that meets patients’ needs have been proved effective in improving patients’ performance in outcomes, knowledge on a disease, and facilitation of decision making [5]. Patient education was strongly recommended by 12 of 15 evidence-based practice guidelines included in a systematic review [6]. Distinct from providing health information alone, evidence-based patient education, a systematic approach combining current medical best evidence, are provided for patients to help understand a disease and its progressive nature, and the management alternatives and protection strategies to facilitate self-care [7, 8]. A recent published trial reported [9] that the knowledge uptake was significantly improved in patients receiving a poster summarizing a clinical practice guideline on conservative treatment options for knee osteoarthritis compared to that in usual care group. A more recent review [10] linked patient education to improved pain and function outcomes compared with usual care in patients with knee osteoarthritis. Despite the documented benefits of patient education, adoption among physicians and compliance with the recommendations of the guideline varies remarkably across different healthcare settings. Studies of patient education have significant heterogeneity in assessing the potential impact of these education programs on health and well-being of participants with osteoarthritis, from which existed inconsistent effectiveness of patient education [11]. Besides, there is always a lack of support in the delivery of patient education, which aims to improve outcomes for patients with osteoarthritis [11]. Two studies recommended that patient education with incorporation of recommendations in clinical practice guidelines and decision-making support has the potential to minimize variation in delivery of care [12, 13]. The development and application of such education tools has huge values in improving patient comprehension and compliance with current practice guidelines.

To elicit maximum impact, electronic health (eHealth), defined as “the use of information and communication technologies for health” by WHO [14], is an alternative forum for the delivery of patient education. Given the prevalence of eHealth in healthcare, introducing patient education programs by using the technology provides tremendous flexibility in disseminating health information, where participants have the choice to access information at any given time without the limitation of location [15]. The positive role of eHealth acting at improving some self-management and adherence to treatment in patients with various diseases has been well recorded [16]. Accumulating evidence indicated that self-management and exercise programs for knee osteoarthritis powered by eHealth approaches significantly improved pain, physical function and quality of life compared to usual care [8, 17]. Similar effects are expected in the patient education of knee osteoarthritis. But for some participants using the eHealth intervention in an undesired way, the diminished effect of these interventions was reported, into which gaining an insight should become one of main focuses in any research involved eHealth interventions [18]. Therefore, designing an eHealth intervention tool incorporating of advanced feedback mechanism like regular reminders and active strategies is necessary. However, a study investigating the effect of a patient education program incorporating the recommendations of clinical guidelines (e.g., OARSI guidelines for the non-surgical management of knee osteoarthritis) with decision-making support through an eHealth approach (developed with participants actively involved) on patients’ perception of knee osteoarthritis as a disease and treatment options, satisfaction and compliance to treatments has not been performed in a population with knee osteoarthritis, specifically for whom live in Southwest China (with the highest prevalence rate, especially in rural areas and communities).

## Methods

### Aim

The primary objective of this study is to evaluate the impact of a physiotherapist-delivered eHealth patient education tool incorporating the recommendations of clinical guidelines (OARSI and COA guidelines) [19, 20] on patient knowledge, to what extent patients with knee osteoarthritis understand the condition and the efficacy of non-pharmacological treatment options.

The secondary objective is to assess patient satisfaction during the process of using the eHealth patient education tool in patients with knee osteoarthritis.

### Study design

This study will be a prospective randomized controlled trial (RCT) comparing an eHealth patient education tool to usual care for knee osteoarthritis. This protocol has been designed according to the Standard Protocol Items: Recommendations for Interventional Trials (SPIRIT) statement [21]. A completed SPIRIT checklist can be found in Additional file 1. In addition, we have used Tidier checklist [22] to help report our intervention section and the checklist could be found in Additional file 5.

### Participants and setting

We will recruit 216 participants referred to the outpatient physiatry/physiotherapy clinic at West China Hospital, Sichuan University in Southwest China. Ethics approval was obtained from Ethics Committee on Biomedical Research, West China Hospital of Sichuan University, and prospectively registered on the Chinese Clinical Trials Registry (ChiCTR2100051083) registered 12.09.2021. Potential participants will be identified from clinic schedules and asked on site to assess their eligibility and to obtain written consent.

To be included, potential participants must present with one of the following: (1) be aged over 45 years, (2) have knee osteoarthritis (Kellgren-Lawrence grade 2 or greater) with symptoms lasting for at least 3 months, (3) is able to provide informed consent, (4) be fluent in verbal and written Chinese, (5) with adequate hearing and eyesight, (6) own an internet-capable device and with access to internet, (7) is not included in the waitlist of knee replacement surgery, (8) be in an independent ambulatory status.

Potential participants will be excluded if they have any of the following: (1) not able to read or speak Chinese, (2) had a history of clinic visits or an appointment with any physician/therapist/healthcare professional for evaluation of knee osteoarthritis, (3) had a diagnosis of fibromyalgia or a systematic arthritic condition, (4) had a history of surgery related to knee, hip and other joints.

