### Randomization and allocation

Eligible participants will be randomized with a one-to-one intervention allocation to the intervention (*n* = 108) or usual care (*n* = 108) group at the time of consent. Allocation concealment will be blinded and performed in the order of recruitment using a computer-generated random allocation schedule operated at the Centre for Biostatistics, Design, Measurement and Evaluation (CBDME) of West China Hospital, Sichuan University by a senior statistician after consent has been obtained. Random permuted blocks of sizes 4 or 6 will be employed to ensure participants are allocated to each group equally. Participants, research coordinators, and the eHealth physiotherapist will be notified, via a sealed opaque envelope, on which group the participant has been randomly assigned.

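### Inclusion is written as meeting one of eight criteria, which contradicts the population, delivery and outcome collection described elsewhere; most likely a drafting error

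*Protocol article*

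**What the plan says.** The inclusion rule is in the Participants and setting section of the protocol article: "To be included, potential participants must present with one of the following: (1) be aged over 45 years". The items that follow include "2) have knee osteoarthritis (Kellgren-Lawrence grade 2 or greater) with symptoms lasting for at least 3 months", "3) is able to provide informed consent" and "6) own an internet-capable device and with access to internet". The others are fluency in Chinese, adequate hearing and eyesight, not waiting for knee replacement, and walking independently.

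The exclusion paragraph directly below uses a different connector, one that suits exclusions: "Potential participants will be excluded if they have any of the following: (1) not able to read or speak Chinese". Its other three items are a previous visit or appointment for evaluation of knee osteoarthritis, fibromyalgia or a systemic arthritic condition, and previous joint surgery.

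The Abstract describes the population without qualification: "We will recruit 216 patients diagnosed with knee osteoarthritis from the outpatient physiatry/physiotherapy clinic". The Aim and Study design sections also frame the trial in knee osteoarthritis.

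**The concern.** Eligibility criteria define the population to which the trial's conclusion applies. The connector printed here makes the eight items alternatives, although they make sense only together: an age limit, a disease definition, capacity to consent and access to a device cannot sensibly replace one another. If the sentence were followed as printed, the trial could enrol people without the disease under study, and people who can neither open the tool nor complete the online questionnaires. Enrolling someone who fails, for example, the radiographic grade would not be a deviation from the published text, and a reader trying to reproduce or audit the population could not tell which criteria bind.

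**Working it through.** The article gives no figure to reproduce here, so this is a check of logic and of consistency between sections.

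**Step 1: the rule as printed.** With inclusion items I1 to I8 and exclusion items E1 to E4, a person is eligible if (I1 or I2 or … or I8) and not (E1 or E2 or E3 or E4).

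**Step 2: a test case.** Take a referred person aged 46 who reads and speaks Chinese, has no knee osteoarthritis and no internet device, and has no previous knee osteoarthritis visit, no fibromyalgia or systemic arthritis and no joint surgery.
- As printed: I1 is true, so inclusion is met. E1 to E4 are all false. The person is eligible.
- With all items required: I2 and I6 are false. The person is not eligible.

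**Step 3: what the list does under the literal reading.** Staff obtain written consent at screening ("asked on site to assess their eligibility and to obtain written consent"), and allocation is made "by a senior statistician after consent has been obtained". Everyone who reaches randomization has therefore consented and meets item 3. Under the literal rule item 3 alone is sufficient, so the inclusion list would screen out nobody who gets that far.

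**Step 4: does other text make each item mandatory?**

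| Inclusion item | Required elsewhere in the article's text? |
|---|---|
| 1. Age | No |
| 2. Knee osteoarthritis, radiographic grade, symptom duration | Diagnosis: yes (Abstract, Aim, Study design). Grade and duration: no |
| 3. Able to consent | Yes: consent precedes allocation |
| 4. Fluent in Chinese | In part, through the first exclusion |
| 5. Hearing and eyesight | No |
| 6. Device and internet access | Not as a requirement. Implied by the WeChat tool and video consultation (eHealth intervention group) and the online questionnaires (Outcome assessment) |
| 7. Not waiting for knee replacement | No; the fourth exclusion concerns past surgery |
| 8. Independent walking | No |

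**Step 5: reading the sections together.** The diagnosis and the internet requirement conflict with the literal rule, so the article contradicts itself on both. Items 1, 5, 7 and 8, and the grade and duration in item 2, rest on the faulty sentence alone.

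**The case against.** The strongest reply is that this is an obvious slip which no clinic would follow. Under the literal rule, not being on a surgical waiting list would qualify almost anyone, and the Abstract and objectives say plainly that the participants have knee osteoarthritis. The text is also a journal article that condenses a fuller protocol, and the screening form and registry entry are not shown, so nothing establishes that staff work from this wording. Most of this stands. It is very probably a drafting error, and there is no evidence that anyone has been or will be enrolled wrongly. It does not remove the point. The sentence is a stated eligibility rule, not a detail left out for brevity, and the rest of the article recovers only part of what was meant.

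A reader might infer more than the documents support, in three ways.

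- **That people unable to consent could enter.** They could not: the consent steps in the Participants and setting and the Randomization and allocation sections stand apart from the inclusion list.
- **That the trial deliberately admits people without the disease.** The Abstract, Aim and Study design say otherwise, so this is a contradiction and not a design choice.
- **That power falls by a calculable amount through dilution.** The article gives no fraction of ineligible entrants, so any percentage would be invented. The mechanism fits poorly too. Outcomes are collected online, so people without internet access would mostly have missing outcomes and would not be observed with zero benefit. Participants who cannot attend the consultation are in any case to be excluded after three contact attempts. For people without knee osteoarthritis, nothing in the article shows that they would gain less knowledge, which is the primary outcome.

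**Conclusion.** The inclusion sentence is wrong as written and should be corrected. It makes eight joint requirements into alternatives, the exclusion list does not repair it, and it contradicts the stated population, the mode of delivery and the mode of outcome collection. Its size is the extent of the ambiguity: four items, and the grade and duration parts of a fifth, have no other support in the text. No loss of power or bias in the treatment comparison is claimed, and the sample-size calculation is unaffected. The conclusion assumes that neither the flow chart nor the additional files, which were not available for this check, restate the criteria as jointly required. If they do, the article's sentence still needs correcting to agree with them.

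**What to change.** Reword the opening of the inclusion list so that potential participants *must meet all of the following*, and leave the exclusion wording as it is. Then check that the screening form and the registry entry do not carry the one-of wording, and correct them if they do. The cost is a few words and, under the article's own section on ethical considerations, resubmission of the change to the ethics committee and an update of the registry. Sample size, randomization and analysis need no change on this account.

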### Randomization and allocation

Eligible participants will be randomized with a one-to-one intervention allocation to the intervention (*n* = 108) or usual care (*n* = 108) group at the time of consent. Allocation concealment will be blinded and performed in the order of recruitment using a computer-generated random allocation schedule operated at the Centre for Biostatistics, Design, Measurement and Evaluation (CBDME) of West China Hospital, Sichuan University by a senior statistician after consent has been obtained. Random permuted blocks of sizes 4 or 6 will be employed to ensure participants are allocated to each group equally. Participants, research coordinators, and the eHealth physiotherapist will be notified, via a sealed opaque envelope, on which group the participant has been randomly assigned.

### Blinding

Due to the characteristic of the research, participants and physiotherapists will not be blinded to group allocation and will be aware of the alternative treatment options. The study hypotheses will be blinded to participants. The researcher conducting the data collection and analysis, however, will be blinded to treatment allocation.

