### Usual care group

The control group will receive usual care including the wide range of care practices provided in the outpatient clinic at West China Hospital which are unrestricted by study protocols, which is in contrast to standard care may not reflect real-world care [23]. Participants in this group will be required to record treatment received using a log sheet weekly over the course of the study period. The common practice consists of a visit to a physiatrist or physiotherapist at outpatient clinic, verbal information about knee osteoarthritis and treatment options, prescription of pain medication, may involve physical or occupational therapy (e.g., manual therapy, physical agents) and advice about home exercises. All participants in the control group will be contacted via telephone or WeChat messenger (Tencent Holdings Ltd., Shenzhen, China) by an assistant who will provide instructions for the participant on how to finish the follow-up questionnaires and access the planned care they were seeking for knee osteoarthritis.

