### eHealth intervention group

Participants assigned to the intervention group will, in addition to usual care, receive an invitation QR code via WeChat messenger to access the eHealth patient education tool built within the WeChat mini programs platform. Participants register themselves using a username and password. The intervention includes instructions on how to efficiently use the tool, information detailing the knowledge of knee osteoarthritis and the recommendations of clinical guidelines including level of evidence supporting each recommendation [24], and advice on healthy lifestyle, in a scheduled video conference with a physiotherapist using Tencent Meeting app (Tencent Holdings Ltd., Shenzhen, China) on a smartphone, a tablet or computer. Participants will be provided with a welcome brochure with an overview of the intervention components, and instructions on how to register and use the eHealth patient education tool and Tencent Meeting app (Web browser, Android or iOS app) at home. The intervention will be delivered within 7 days after the randomization, during which the video consultation with a physiotherapist will last up to 90 min according to the patient’s preference. Automatically generated push notifications within WeChat messenger will be sent to motivate participants to review the information and use the tool twice a week after the consultation for at least 6 months. Additionally, participants have the possibility to get help from the coordinators or via the study hotline regarding any technical problems when using the tool.

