An iterative method of collaboration-based persuasive design between healthcare providers and patients is employed to the development of the eHealth patient education tool [18]. In brief, a focus group (*n* = 6, involved 3 patients with knee osteoarthritis, 2 physiotherapists and 1 physiatrist) was initially conducted in two phases during the development process, in which healthcare providers met at Phase I to provide input on the eHealth prototype regarding design and content and patients were invited to Phase II to discuss with healthcare providers regarding literacy demands and usability. Then a pilot-testing of the developed tool will be done among healthcare providers and patients (with a total of 20 participants) in a similar way to the focus group, and the testing version could be found in Additional file 2. The tool includes the following features:**Education Center:** information on knee osteoarthritis and treatment options (details could be found in Additional file 2), based on the recommendations of clinical guidelines; exercise advice and videos; physical activity and well-being advice.**Personal Information:** the option to record demographic data and history of knee osteoarthritis.**Self-Management:** self-monitor symptoms during the study; log the planned care received for knee osteoarthritis and other comorbidities.**Schedule and Plan:** set reminders and develop a calendar for the scheduled consultation, and assessments.**Communication and Help Center:** contact with an assigned physiotherapist or healthcare professional; an overview of the educational tool.

Participants who cannot attend the consultation will be excluded after contact has been attempted three times. One day after the consultation with the physiotherapist, all participants will receive the follow-up questionnaires on their WeChat. A reminder will be sent if participants are found non-responding after 1 week. Intervention fidelity will be assessed to rate the degree of involvement of a patient within 24 h after the physiotherapist-delivered consultation. As a participant reads information or watches a video, analytics built into the server website will collect data on what type of information and how long the participant spent on that. The chief research coordinator, program developer, and research assistance conducting data collection have access to the website and are able to view the analytics for each participant.

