#### Other measures

Participants’ demographic data, history of diseases and health behavior information will also be collected. Potential “inadequate health literacy level” in participants will be screened using 3 questions: “how confident are you filling out questionnaires by yourself?” (“Confident with Questionnaires”), “Do you need someone to help you read? If yes, how often?” (“Read Assistance”) and “Do you have obstacles learning about your medical condition due to your inability to read? If yes, how often?” (“Problem Reading”) [28, 29]. In the process evaluation, measures of recruitment rate, attendance and follow-up rate will be monitored and recorded. Reasons for exclusions, declining participation and the drop-out of participants will be noted through the trial.

Participants in the eHealth intervention group will receive additional questions on the usability of the tool, including 13 closed questions and 3 opened-ended questions [30] and details of the questionnaire could be found in Additional file 4. Web-based analytics generated by the educational tool will be used to assess the utilization of the tool, which include data on content with which they engage, length of time spent on different content, and satisfaction ratings or feedback.

The measure of opinion and perspectives for participating the trial will be assessed via a phone- recorded interview (semi-structured) in both the eHealth and usual care group with the interviewee’s permission, for which a guide with open questions will be used to provide structure. The phone call will be made by a researcher who have experiences in qualitative interviews and is independent of the conduction of this trial. Two researchers (independent of the conduction of this trial) will be instructed by the interviewer to independently read and code transcribed texts line-by-line, from which codes generated will be sorted into themes and discussed to gain an overall understanding of any issue on difficulties and barriers to complete the trial. Any discrepancy will be resolved by the interviewer (senior researcher). During the trial, adverse events, medications and any other care received will be recorded using a log sheet, a sample could be found in Additional file 3.

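### Data collectors are described as blinded, yet staff collecting data can view usage analytics of a tool that only the intervention arm receives

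*Protocol article*

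**What the plan says.** The Blinding section discloses that participants and physiotherapists know the allocation. It then makes one claim of masking: "The researcher conducting the data collection and analysis, however, will be blinded to treatment allocation".

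Other sections bear on that claim:

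- **Who gets the tool** (eHealth intervention group): "Participants assigned to the intervention group will, in addition to usual care, receive an invitation QR code via WeChat messenger". The code opens the education tool. The usual care group has no such access.
- **What the tool records** (same section): "analytics built into the server website will collect data on what type of information and how long the participant spent on that".
- **Who can see those records** (same section). Three roles are listed: the chief research coordinator, the program developer, and a third described thus: "research assistance conducting data collection have access to the website and are able to view the analytics for each participant".
- **Arm-specific questionnaires** (Other measures): "Participants in the eHealth intervention group will receive additional questions on the usability of the tool". There are 13 closed and 3 open items.
- **Who is told the allocation** (Randomization and allocation): "Participants, research coordinators, and the eHealth physiotherapist will be notified, via a sealed opaque envelope, on which group the participant has been randomly assigned".
- **Contact with controls** (Usual care group): they are contacted by phone or WeChat by "an assistant who will provide instructions for the participant on how to finish the follow-up questionnaires".
- **The analyst** (Data integrity and monitoring; Statistical analysis): both sections describe a statistician who does not know the allocation.

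**The concern.** The Blinding section gives staff who collect data a property that the access rule takes away. Per-participant usage records from a tool given to one arm work as an allocation list for that arm. A final report repeating the Blinding section would claim masked data collection, and readers judging risk of bias would credit the trial with a safeguard it did not have.

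What is at stake in practice is contact between staff and participants around the questionnaires. Staff who know the arm could word instructions or follow up non-response differently, even without intending to. That could produce different response rates in the two arms and, less directly, different scores. Satisfaction and trust in the physiotherapist, the secondary outcomes, are also self-reported around that contact.

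**Working it through.** No alpha, power, effect size or sample size enters this point, so there is nothing to calculate. The check sets the sections side by side.

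1. **Is data collection claimed to be blinded?** Yes, in the Blinding section. The sentence covers both collection and analysis.
2. **Can staff who collect data see individual tool analytics?** Yes. The eHealth section identifies the third role with access by its function, which is data collection, and says the view is for each participant.
3. **Do the analytics exist in one arm only?** Yes. The invitation goes only to participants assigned to the intervention, so a usage record implies intervention allocation.
4. **Does the reverse hold, so that no record implies control?** Not always. Participants register themselves with a username and password. Someone assigned to the intervention who never registers may leave no record. The inference is firm from a record to the intervention arm and only probable from no record to control.
5. **Is there a second route?** Yes. The usability items go to the intervention arm alone, so anyone handling those returns learns the arm without opening the analytics. Care received may be a third route. The tool has a log of planned care, while controls fill in a weekly log sheet. Other measures also mentions a log sheet without naming an arm, so the article leaves open how far the care logs differ by arm.
6. **Does any section mask the analytics, or separate those who view them from those who collect outcomes?** No section of the article describes either.
7. **Does the contradiction reach the analyst?** No. Two other sections state that the statistician is blinded, and the access list does not include the statistician.

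Steps 1 to 3 are enough: the Blinding sentence and the access sentence cannot both hold for data collection. Steps 4 and 7 set the limits of the point. Step 5 shows that withdrawing website access alone would not restore the blinding.

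**The case against.** The best case on the other side has four parts.

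**The two sentences may describe different people.** The Blinding section speaks of a researcher who collects and analyses; the eHealth section speaks of research assistance. A condensed article need not set out the delegation of roles. This stands only as a possibility. Both sentences identify the person by the same function, and nothing in the article separates them. If they are different people, the article needs to say so.

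**Coordinators and the control-arm assistant prove nothing.** This stands. A reader might infer a further contradiction from "Participants, research coordinators, and the eHealth physiotherapist will be notified, via a sealed opaque envelope, on which group", or from the assistant who contacts controls. But the Blinding section never says coordinators are blinded. Nor does the article say that this assistant collects outcome data.

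**There is little route to bias in the primary outcome.** This largely stands. The knowledge questionnaire is completed through an online link, has predefined correct answers, and is not rated by an observer. That participants are unblinded is already disclosed. A reader might go further and infer that unblinded staff pursue non-responders or help with the knowledge test. The text does not support that. It says that a reminder goes out after 1 week, without naming a sender or any difference by arm, and the assistant explains how to finish the questionnaires. Different handling by arm is a risk here, not something the plan describes.

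**Nothing shows that allocation is exposed for everyone.** This stands. A reader might conclude that the arm of all 216 participants can be deduced. That needs every one of the 108 intervention participants to leave a record, which self-registration does not guarantee, and it needs usernames to be linkable to outcome records, which the article does not describe.

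**Conclusion.** The point holds for data collection. As written, the plan claims blinding for a function whose staff can view records that reveal intervention allocation, and the intervention-only usability questions reveal it again.

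A reader might infer that the stated blinding fails altogether. The documents do not support that, since the blinded statistician is stated twice and is not contradicted.

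The consequence is moderate. The effect on the primary knowledge score is probably small. The more plausible consequence is different contact, and hence different response, between arms. No size can be given for it, because the article reports nothing on response by arm or on how contact varies. The certain consequence is an inaccurate blinding statement carried into the final report.

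The conclusion rests on two assumptions: that the staff named in the access sentence are those meant in the Blinding section, or include them; and that a usage record can be linked to a person, as the wording on viewing analytics for each participant implies. The correction should be made because the error is clear and cheap to remove. It does not threaten the primary analysis.

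**What to change.** Reconcile the Blinding section with the access sentence in one of two ways.

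**(a) Make the claim true.** Until the 6-month (T4) data are locked, staff who collect outcome data should have no access to the analytics and should not handle the usability returns or the tool's care logs. If the weekly log sheets come from controls only, the same separation should apply to them. Use one scripted set of questionnaire instructions and one reminder text, identical in both arms. The cost is a change of website permissions, a separate handler for the arm-specific returns, and a few sentences of protocol text. The small downside is that data-collection staff cannot check tool usage during follow-up; the program developer or chief coordinator, who already have access, can do so.

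**(b) Make the claim smaller.** Reword the Blinding section to say that data collectors are not blinded, that outcomes are self-reported by participants who know their arm, and that the blinding claim is limited to the statistician. This costs only wording. It leaves the scope for different contact in place, so the identical scripts in (a) are worth adopting here too.

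Withdrawing analytics access while still calling the data collectors blinded would not be enough, because the usability returns would still show the arm.
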